## Abstract

**Background:**

The distal radius fracture (DRF) is a common fracture, with the majority of these fractures being stable. Of all diagnosed fractures, 17% is a DRF, of which a large part is extra-articular and one-third is non-displaced. There is a large variation in treatment advisements for non-reduced DRF. Four to 5 weeks of immobilization is often the usual practice. Existing evidence shows that 1 week of immobilization is safe and does not lead to an increase in secondary displacement. Additionally, shorter immobilization periods may lead to less outpatient clinic visits and less home care for elderly people and may lead to earlier return to work and other social activities. Therefore, shorter immobilization periods for non-reduced distal radius fractures may also prove to be cost-effective.

In this study, we aim to successfully implement 1 week of plaster cast immobilization for non-reduced distal radius fractures in twelve medical centers and to evaluate the functional outcome and cost-effectiveness.

**Methods:**

This study will be performed using a multicenter randomized stepped wedge design in 12 centers. We aim to include in the study 440 patients with an isolated non-reduced DRF between the age of 18 and 85 years old. The patients in the intervention group will be treated with plaster cast immobilization for 1 week. Acceptability of the study protocol, patient-reported outcomes, quality of life, complications, pain catastrophizing score, pain and patient satisfaction, and cost-effectiveness will be measured. The total follow-up will be 12 months.

**Discussion:**

The strength of this study is the combination of implementing 1 week of plaster cast immobilization for non-reduced DRF and the evaluation of functional outcome, acceptability of the study protocol, and cost-effectiveness in actual practice.

**Trial registration:**

Netherlands Trial Register NL9278. Registered on 17 February 2021

## Background

The distal radius fracture (DRF) is a common fracture. A large part of all diagnosed fractures at the Emergency Department are DRFs, around 17%. One-third of these fractures are non-displaced fractures [1–3].

In recent years, there has been an increased interest in the treatment of DRFs, caused by the increasing prevalence of DRFs and improvements in minimal invasive surgical treatment techniques. However, recent literature mainly focused on treatment options for unstable distal radius fractures, for which several treatment modalities have been advocated [4, 5]. Nonetheless, little attention has been paid to the treatment of the stable DRF. To date, there are only a few studies that have investigated the duration of immobilization for non-operatively treated, stable DRFs [6]. A systematic review (2018) included 12 studies, of which a small part focused on non-reduced fractures. The authors concluded that an immobilization period of 3 weeks or less is equally effective compared to the longer immobilization period and might be associated with better functional outcome [6].

There are several guidelines in the world for DRFs [4, 7]. However, a unified treatment recommendation for non-reduced (minimal and non-displaced) DRFs does not exist. The usual care in the Netherlands consists of 3- to 5-week immobilization for these kinds of fractures. There are several studies that show that the 1 week of plaster cast treatment for a stable DRF is safe and effective [6, 8, 9]. A feasibility study including 40 patients with a non-reduced DRF, randomized in an intervention group (1 week of plaster cast treatment) or control group (4–5 weeks of plaster cast treatment) showed positive results and no secondary displacement. In addition, a trend was shown in the intervention group of having less pain, better functional outcome after 6 weeks, going back to work earlier, higher patient satisfaction, and no differences in complications. Moreover, it appeared that patients preferred a shorter immobilization period (cross-over in eight patients, seven patients went from the control group to the intervention group) [10].

Recent studies have shown that a long period of immobilization is associated to more post-traumatic pain by increasing disuse and kinesiophobia [11–13]. These studies also show that early mobilization after a period of plaster cast may reduce the incidence of post-traumatic pain including complex regional pain syndrome (CRPS).

### Rationale

There is a large variation in treatment advisements for non-reduced DRFs. Existing evidence for 1-week immobilization shows that 1 week of immobilization is safe and does not lead to more secondary displacement. However, there is a lack of evidence on functional outcome, pain and pain medication use, and time to return to activities and work after non-operative treatment for non-reduced DRF. The interest for shorter immobilization periods for these fractures is high, from both professionals as well as patients. Shorter immobilization periods may lead to less outpatient clinic visits and less home care for elderly people and may lead to earlier return to work and other social activities. Shorter immobilization periods for non-reduced DRFs may therefore prove to be cost-effective.

In this study, we aim to successfully implement 1 week of plaster cast immobilization for non-reduced DRF in twelve medical centers and to evaluate the functional outcome and cost-effectiveness for 1 week of plaster cast immobilization compared to the usual care.

### Hypotheses

Our hypotheses in the study are as follows:
One week of plaster cast immobilization may successfully be implemented at the participating hospitals with a good acceptability of the study protocol rate (small number of protocol violations).One week of plaster cast treatment (condition B) will give a lower PRWE score (less pain and better physical function) compared to the usual care group (condition A) for non-reduced DRFs.One week of plaster cast treatment (condition B) will give lower pain scores with less use of pain medication compared to the usual care group (condition A) for non-reduced DRFs.One week of plaster cast treatment (condition B) will lead to earlier optimal functional outcome scores than the usual care group (condition A) for non-reduced DRFs.One week of plaster cast treatment (condition B) will be less costly compared to the usual care group (condition A) for non-reduced DRF.There is no difference in complications for the intervention group (condition B) versus the usual care group (condition A).

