### Measurements

For this study, the following main study parameters are gathered: functional outcome, return to activity, cost-effectiveness, and acceptability of the study protocol.
Patient-reported outcome (functioning and patient satisfaction): It is known that 1 week of plaster cast for a non-reduced DRF is safe. Secondary displacement of the fracture is not significantly different with longer plaster cast treatment [8, 9]. So, the most important question is whether 1-week treatment gives better functional results and higher patient satisfaction. The best measurement method to measure patient satisfaction and functional result is using a patient-reported outcome (PRO) [14]. In addition, PROs are better predictors of participation, such as the ability to return to work or perform daily activities, than more objective clinical measures.The Patient-Reported Wrist Evaluation (PRWE) is specifically designed for wrist and hand functioning. The PRWE is a reliable and valid measure of patient-rated pain and disability for wrist conditions [15, 16]. Furthermore, a validated Dutch version of the questionnaire is available [17]. The PRWE is a measurement with a score from 0 to 100, where 0 is no wrist function problems or pain. The minimal clinical important difference for PRWE is a difference of 11 points [18].The questionnaires will be sent to the patient after 6 weeks and 3, 6, and 12 months.Return to activity will be measured using the productivity costs questionnaire (iCPQ). Questions about return to work, leisure activities, household activities, and pain will be asked. These questions will be asked after 1 and 6 weeks, 6 months, and 1 year.A cost-effectiveness analysis will be performed alongside the stepped wedge trial. The Health care Institute of the Netherlands (ZIN) 2016 guideline for economic evaluations forms the basis of the analysis [19]. Healthcare consumption from inclusion to final follow-up of the patient is measured. This is in line with the measurement pathway of the clinical study. Healthcare consumption is multiplied by unit costs associated with healthcare consumption. Also, productivity-related costs seem to play an important role. Therefore, the societal perspective is the base case. A healthcare perspective is used as the scenario. These will be measured using a selection of questions of the medical consumption questionnaire (iMCQ) and the productivity costs questionnaire (iCPQ). These questions will be asked after 1 and 6 weeks, 6 months, and 1 year. The costs and for example months not working will be compared for the two different condition groups.Acceptability of the study protocol. Measuring the actual time of plaster cast treatment and number of patients who followed the protocol. If not following the protocol (condition A or B), reason for violation of the protocol. The answers to these questions will be gathered at the end of the study by provided information from the hospitals and questions asked to the participating physicians. All patients who gave informed consent will be checked if they follow the correct protocol. If they did not follow the protocol, information will be gathered why the protocol was not followed. Additionally, questions will be asked to the participating centers (local head of research). The questions asked are about feedback to the study, if they will implement the interventional treatment, why they will or will not implement the treatment, what changes to the treatment they would make, etc. The number of protocol violations and comments will be compared for both groups.

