### Power analysis

We used the stepped wedge sample size tool in STATA.

A sample size of 330 patients was calculated with a power of 0.85, alfa of 0.05, and *ICC* of 0.01. We designed the stepped wedge for ten clusters with three patients per cluster per time period (Table 1). We used results from our pilot study for the reference values. The Patient-Rated Wrist Evaluation (PRWE) scores after 6 weeks were used as this will be one of our most important outcomes and have a validated clinical difference score. We used a PRWE score of 35 for the control group and 25 for the intervention group. A difference of around 10 points is needed to reach a relevant clinical difference [18]. In order to account for a 30% loss to follow-up, we aim for a sample size of 440 patients, i.e., four patients per cluster per time.

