### Statistical analysis

Descriptive analyses with median, range, and percentage will be used to describe demographic variables and outcomes such as age and gender. We will analyze the percentage of protocol violations and the willingness to participate from participating patients, hospitals, and physicians using a feedback evaluation. Patients will be asked to give feedback at the end of their follow-up period and physicians will be asked feedback after 6 months and 12 months.

A multivariate linear regression mixed model will be used to analyze the data from the different randomization groups and to account for clustering of repeated measurements within patients and within hospitals and time. We will analyze the effect of the intervention, in comparison with the usual care, on the PROs, return to activity, pain scores, and complication rate. We will adjust for confounding factors such as age, gender, and clinical parameters. The difference in complication rate will be determined using either a Fisher exact or a chi-square test, depending on the order of magnitude of the results. The difference in PCS-4 score, VAS score, and patient satisfaction will be determined using a *t*-test. The analysis will be performed by using the intention-to-treat model (according to the groups to which they were originally designed).

A cost-effective analysis will be performed additionally to the above-mentioned analyses. A budget impact analysis will be performed from various perspectives with the budgetary framework for the care as the base case perspective.

For missing data from patients who fulfilled the study, the available data will be analyzed if possible, for any interesting findings, and otherwise, the missing data will be imputed with replacement values using multiple imputation analysis.

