## Discussion

This publication presents an implementation study with the use of a randomized multicenter stepped wedge design for the use of 1 week of plaster cast immobilization after non-reduced DRF. This study will be used to implement 1 week of plaster cast immobilization in several hospitals. In addition, this study tries to answer the question whether 1 week of plaster cast gives lower PRWE scores, better patient satisfaction, earlier return to work, and lower costs and if it will have the same complication rate.

A limitation of this study is the variability in clinical judgment when to reduce a DRF and thereby the chance of bias due to the surgeon’s decision who expects a high chance of secondary displacement. However, the variability in deciding when to reduce a DRF is part of common daily practice. A second limitation may be the choice for a stepped wedge design instead of a randomized controlled trial. During the feasibility study, we encountered a lot of problems with patient cross-over, difficulty performing the study for the hospitals and a large number of patients who did not want to participate in the study. By using a stepped wedge design, we think the problems with the treatment protocol will be less variable. In addition, the greater variability in deciding when to reduce a DRF leads to the exclusion criteria which will be used in general practice. Therefore, this study will give an answer which can be directly translated into daily practice.

The strengths of this study are the pragmatic nature of this study, the fact that it is an implementation study (using the Dutch guideline) in combination with a comparative study, and the use of a cost-effectiveness analysis. The pragmatic nature of this study, using a stepped wedge design, leads to a very clear protocol to use for every hospital. A clear and easy protocol is necessary as this study is an implementation study. In addition, with this study design, we can include 440 patients in 1-year time. A cost-effectiveness analysis will be performed which will give extra evidence for the effectiveness of 1-week plaster cast immobilization. Other strengths of the study are the validated primary outcome measure (PRWE) and taking into account psychological views of post-traumatic pain using the PCS-4.

As this is an implementation study, we hope the results of this study will be used for the implementation of 1-week plaster cast immobilization for non-reduced DRF nationally.

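### The hypothesis of no difference in complications is paired with an unadjusted test of difference and no margin, so a non-significant result cannot support it

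*Protocol article*

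**What the plan says.** Three places in the protocol article bear on this.

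- **Hypotheses**, last item: "There is no difference in complications for the intervention group (condition B) versus the usual care group (condition A". It stands beside five directional or implementation hypotheses as something the trial expects to support.
- **Discussion**, first paragraph: among the questions the study tries to answer is "if it will have the same complication rate".
- **Statistical analysis**: "The difference in complication rate will be determined using either a Fisher exact or a chi-square test", the choice depending on the size of the numbers. Just before this, after describing a mixed model that accounts for patient, hospital and time, the section says the intervention effect will be analysed "on the PROs, return to activity, pain scores, and complication rate".

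Complications are a secondary outcome. No non-inferiority or equivalence margin, expected complication rate or power for complications is given. The only power calculation is for the wrist score (PRWE) at 6 weeks.

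**The concern.** The Fisher exact and chi-square tests take equal rates as the null hypothesis. A small p-value is evidence against equality. A large one may mean that the rates are equal, or that there were too few events to tell. The test named therefore cannot deliver the conclusion that the hypothesis states, however large the trial is, unless a margin or an interval says which differences have been excluded.

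The tests also treat all patients as independent and pool over calendar time. In this design usual care is concentrated in the early periods and the one-week cast in the late ones. A crude comparison of the two conditions therefore mixes the treatment effect with any time trend, and it ignores correlation within clusters.

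At stake is what may be said about complications at the end. The Discussion hopes that the results will lead to national implementation, and a statement that complications are the same would be part of that case.

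**Working it through.** **1. The plan's own numbers.** Table 1 has 55 usual-care cells and 55 one-week cells, leaving out the transition cells.

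- 110 cells × 3 patients = 330, as in the Power analysis: "A sample size of 330 patients was calculated with a power of 0.85, alfa of 0.05".
- 110 cells × 4 patients = 440, or 55 × 4 = 220 per condition.
- After the stated 30% loss: 440 × 0.70 = 308, or 154 per condition.

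The power of 0.85 applies to the wrist score. Its standard deviation is not given. A standard stepped-wedge variance (fixed periods, ICC 0.01, two-sided 0.05, transition cells omitted) returns 0.85 if the SD is 20, which is plausible. Nothing in that calculation concerns complications.

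**2. Power of the planned test to detect a doubling.** The usual-care rate is not in the document, so a range is assumed. The method is exact Fisher power by enumeration, two-sided 0.05, counting rejections that show an excess under the one-week cast.

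| Assumed rates, A → B | 220 per condition | 154 per condition |
|---|---|---|
| 2% → 4% | 15% | 9% |
| 5% → 10% | 45% | 31% |
| 10% → 20% | 81% | 64% |
| 20% → 40% | over 99% | 96% |

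Power for a doubling reaches 50% at these usual-care rates:

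- normal approximation (close to the chi-square test): 4.9% with 220 per condition, 6.7% with 154;
- exact Fisher: 5.5% with 220, 7.6% with 154.

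The threshold is thus roughly 5% to 7%. Below it the planned test misses a doubling more often than not; above it, it does not.

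**3. What an interval would exclude.** With equal true rates p and n per condition, the 95% half-width for the risk difference is 1.96 × √(2p(1 − p)/n).

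- p = 5%, n = 220: 1.96 × √(0.095/220) = 4.1 points
- p = 5%, n = 154: 1.96 × √(0.095/154) = 4.9 points
- p = 10%, n = 220: 1.96 × √(0.18/220) = 5.6 points
- p = 10%, n = 154: 1.96 × √(0.18/154) = 6.7 points

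**4. Effect of cluster and period adjustment.** For the Table 1 layout with ICC 0.01, the variance of the adjusted effect is 2.30 times that of a simple two-group comparison at 3 patients per cell, and 2.37 times at 4 per cell. The standard error ratios are √2.30 = 1.52 and √2.37 = 1.54. This factor is derived for a continuous outcome. If it carries over, the half-widths with 220 per condition become about 6.3 points at 5% and 8.6 points at 10%. The usual-care rate at which a doubling is detected half the time then rises to about 10.5% at 4 per cell, or 12.9% at 3 per cell.

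**5. What a non-inferiority claim would need.** Illustration only, because the document names no margin. To exclude a 5-point excess with equal true rates (one-sided 0.025, 80% power, no clustering), 299 patients per condition are needed at a rate of 5% and 566 at 10%, against 220 planned. At 2% the figure is 124.

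**The case against.** Four arguments count on the other side.

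*The article never says that a non-significant result will be read as equal safety.* That is correct. The hypothesis is an expectation, and the Discussion poses a question, not a decision rule. A reader might infer the misreading from the Measurements section, where safety is supported by the remark "Secondary displacement of the fracture is not significantly different with longer plaster cast treatment". That makes it plausible, but it is not protocol text. What stands without it is that hypothesis and test do not fit each other.

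*The trial may be well able to detect a doubling.* This also stands, as a condition. A reader might infer that a doubling would usually be missed. The documents do not support that in general, because they give no rate, and at 10% against 20% the unadjusted test has 64% to 81% power. The outcome combines a complication checklist, criteria for complex regional pain syndrome and secondary displacement over 12 months, so a higher rate cannot be ruled out. Losses may also be below 30%, since clinical records are used as well as questionnaires; the column for 220 covers that case.

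*An adjusted analysis is already mentioned.* It is, in the list that follows the mixed model, so the Fisher or chi-square test is not the only analysis named. But the section then assigns the complication comparison to the unadjusted test, and neither analysis comes with a criterion for no difference.

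*Complications are secondary, and interval reporting belongs in an analysis plan.* The first part limits the weight of the point: the article treats safety as already shown and calls function and satisfaction the main question. The second would hold if the article were silent. It is not, because it fixes both the hypothesis and the test.

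**Conclusion.** The point holds as a mismatch between hypothesis and analysis, and that part needs no assumed rate: an unadjusted test of difference without a margin cannot support a conclusion of no difference or of the same complication rate, and it disregards clustering and calendar period. The two statements on complication rate in the Statistical analysis section also have to be reconciled.

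How much a non-significant result would hide depends on a rate that the article does not give. The risk of missing a doubling is high at assumed rates of 5% or less (power at most 45%) and moderate to low at 10% with the unadjusted test. It is greater under an adjusted analysis, if ICC 0.01 and the continuous-outcome factor of about 1.5 apply to complications. Good power would not rescue the inference, because non-significance without a margin still does not establish equality. For a secondary outcome with a cheap remedy, this should be changed but does not threaten the trial.

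**What to change.** Before recruitment, which the Trial status section says had not started:

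1. Reword the sixth hypothesis as estimation: the trial will estimate the difference in complication risk, one-week cast minus usual care.
2. Replace the Fisher or chi-square comparison with the cluster- and period-adjusted risk difference and its 95% confidence interval, and make the mixed-model sentence consistent with this.
3. Report the largest excess that the interval excludes, and do not claim equality from a non-significant p-value.
4. Claim that the one-week cast is not worse only if a margin was fixed before recruitment and the upper limit lies below it.

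Steps 1 to 3 need no extra patients or data; they change wording and the analysis model. The cost is a wider interval and possibly a weaker statement on safety. Step 4 is more than wording: a margin must be justified, and at rates of 5% or more the trial would be too small for the 5-point margin used above as an illustration.
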